### Sample size and power analysis

We conducted a power analysis based on the proposed sample size of 144 dyads. Our analysis of feasibility and safety (Aim 1) will use descriptive statistics and comparisons between arms without predetermined expectations regarding statistical power. In contrast, data related to Aims 2 and 3 will be analyzed using the intention to treat ( ITT) principle [48,49]. Power calculations, performed assuming a significance level of 0.05, 90% retention, and no contamination, indicated that we have sufficient statistical power to detect changes in intermediary outcomes , that is, indicators of DILs’ and MILs’ empowerment (e.g., proportion of DILs who report that wife beating is unjustified). If 45% of DILs in the control arm report that wife beating is unjustified [27], we will be able to detect a relative risk of 1.6 with 88% power. Due to resource and time constraints of a phase 2 trial, we did not power the trial to detect a significant effect on DV. Nevertheless, we estimated power calculations for DV among DILs during the first 6 months postpartum based on the literature. Given the proposed sample size, we will be able to detect a relative risk of 0.5 with power ranging from 23% to 95% when the proportion reporting DV in the control arm ranges from 20% to 50%.

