Building on previous intervention trials that have focused on vulnerable populations and included detailed risk appraisals (such as measures of depression and experience of physical harm), we established a safety monitoring system that centered around two types of safety-related events: safety alerts and adverse events. Safety alerts constitute “red flags.” They are events that may pose safety risks to participants, but may not involve participants directly, or if they do, are unlikely to be related to study participation or not considered to be severe. Examples of safety alerts include staff witnessing a family disagreement or conflict that is unrelated to the study, participant report of a minor altercation at home due to study participation, gossip in the community regarding study objectives, or enquiries about the study by family members. Miscarriages among DILs and illness episodes among MILs may be classified as safety alerts if they are determined to be unrelated to study participation. Safety alerts may warrant investigation by the study team to determine relatedness to study activities through discussion with participants and discreet gathering of information in the community (without jeopardizing participant confidentiality). Safety alerts may result in heightened monitoring of interactions with one or more participants, and will be reported to the IRB every six months.

Adverse events are defined as unexpected, unfavorable, and serious events such as serious injury, self-harm, hospitalization, or pregnancy loss that are temporally associated with and likely to be related to study participation. Adverse events will be reported to the IRB within 24 to 48 hours, and may result in substantive changes in the research protocol or other corrective actions in order to protect the safety, welfare, or rights of participants.

Definitions of safety alerts and adverse events were finalized through discussion and consensus among the study team and members of a two-person data and safety monitoring committee (DSMC) established for the study. Staff will be required to report all events without delay to the project director and principal investigators who will be responsible for classifying the event, developing appropriate responses, and reporting to the IRB and DSMC. All events will be recorded on an Incident Occurrence Reporting Form.

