### Randomization

Consenting dyads will be randomized as pairs on completion of the baseline assessment. Within each site, dyads will be randomized to ensure treatment balance after every 20 randomizations. The study statistician will employ a pseudo-randomizer software package to determine dyad treatment assignments and provide a series of sealed opaque randomization envelopes to study staff with one envelope per dyad. The participant IDs will be printed on the outside of the envelope, and the assigned study arm will be printed on a card contained in the envelope. A designated staff member at each center will open envelopes in sequential order of participant ID. Post randomization, the project director will ensure that the staff designated to facilitate intervention sessions do not conduct follow-up interviews or vice versa, and interviewers will not have access to information on treatment assignment.

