### Intervention and control conditions

Dyads will be randomized to the control arm and receive standard care or to the intervention arm and receive standard care plus the *Dil Mil* intervention. Standard care for DILs includes primary care and access to DV-related support services [45,46]. For MILs, we will offer a comprehensive health examination including a gynecological exam and screening for diabetes and hypertension, along with appropriate information, prescriptions, and/or referrals. We will routinely offer DV-related resources, such as information, counseling, and referrals to all participants, DILs and MILs, regardless of study arm.

The intervention, which will be implemented during the second and third trimesters of the DILs’ pregnancy, consists of 2 half-day group sessions with DILs, 5 half-day group sessions with MILs, and one joint half-day session with DILs and MILs. *Dil Mil* is delivered at the health center to small groups consisting of 12 DILs or MILs (i.e., 6 groups of 12 individuals), except for the joint session in which DILs and their MILs participate together.

The curriculum is based on participatory learning and action principles and uses stories, role-play, and discussion to enhance participants’ knowledge, skills, and social support (see [36] for details). Facilitators will encourage participants to critically analyze their relationships and to develop and implement responses appropriate to their families and communities. The group education sessions with MILs will focus on the physical and psyschosocial dimensions of growing older and the impact of life experiences including experience of DV and familial relationships on their current health status. Based on these discussions, MILs will be encouraged to reflect on the health of daughters and DILs. Thus, by beginning and grounding discussions of DV and women’s health in personal experiences and by addressing MILs’ health concerns, we expect to reduce the risks of the intervention to participating DILs.

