### Quantitative assessments and analytic plan

Quantitative data on feasibility (including recruitment, retention, adherence, and contamination) and safety of the intervention will be gathered through study records pertaining to recruitment, adherence, retention and safety. Data on empowerment of DILs and Mils (knowledge about safety and the links between DV and health, gender-equitable attitudes, decision-making skills, communication and social support, and resistance to DV) and incidence of DV and related health outcomes (e.g., quality of life, anxiety and depression, and maternal and infant health) will be gathered by research interviewers not involved in intervention implementation through face-to-face interviews. Interviews with DILs and MILs will be conducted individually at enrollment and 3 months and 6 months postpartum. Measures were chosen based on our theoretical approach and drawn from instruments used in our previous research, the Indian National Family Health Survey and studies of GBV and health in India and elsewhere (Table 3). Questions were selected keeping in mind the need to minimize study participation-related risks. For example, questions regarding MILs’ perpetration of violence will only be posed to DILs, and MILs’ experience of DV will also be posed in order to monitor safety of the intervention.

**Table 3 T3:** Measures

**Measure**	**DIL**	**MIL**

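### Recorded safety events are compared between arms, but only the intervention arm has extra staffed sessions in pregnancy, so the counts are open to unequal ascertainment

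*Protocol article*

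**What the plan says.** All references are to the protocol article.

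- **Comparison.** Sample size and power analysis: "Our analysis of feasibility and safety (Aim 1) will use descriptive statistics and comparisons between arms", with no power target.
- **Measure.** Table 3 lists safety as the number and nature of safety-related events, for DILs and MILs.
- **Source.** Quantitative assessments and analytic plan: data on the "safety of the intervention will be gathered through study records pertaining to recruitment, adherence, retention and safety". The same paragraph assigns empowerment, domestic violence and health outcomes to face-to-face interviews.
- **Route into the record.** Safety monitoring: "Staff will be required to report all events without delay to the project director and principal investigators". Safety alerts include small family altercations over the study, community gossip and relatives' questions.
- **Timing of randomisation.** Randomization: "Consenting dyads will be randomized as pairs on completion of the baseline assessment".
- **Contacts in both arms.** "Interviews with DILs and MILs will be conducted individually at enrollment and 3 months and 6 months postpartum". Safety monitoring also describes antenatal assessments for DILs, on-site counselling, an information counter and an instruction to contact the project director about threats to safety. None is limited to one arm. MILs are offered a health examination in the account of standard care.
- **Contacts in the intervention arm only.** Intervention and control conditions: the intervention "consists of 2 half-day group sessions with DILs, 5 half-day group sessions with MILs, and one joint half-day session with DILs and MILs", and it "will be implemented during the second and third trimesters of the DILs" pregnancy.

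**The concern.** An event is counted only if a staff member sees it or is told of it. The opportunity for that differs by arm, and the difference falls in one period. Between baseline and 3 months postpartum, controls have no scheduled research interview, while intervention women spend several half-days with facilitators who build rapport and discuss violence. Two arms with the same true risk could then produce different numbers of recorded events.

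This matters because safety is part of Aim 1, and evidence of safety is one of the criteria in the Discussion for moving to phase 3. The Discussion names backlash from the husband and his family as the harm to watch for. An excess of recorded events in the intervention arm could reflect backlash or better detection, and the count alone would not separate them.

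**Working it through.** The article gives no contact count and no detection rate, so there is no stated figure to reproduce. The contact counts below follow from the article. The ascertainment model rests on assumptions.

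**1. Sessions and follow-up interviews only**

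- DIL, intervention: 2 separate + 1 joint session + 2 interviews = 5. Control: 2. Ratio 5/2 = 2.5.
- MIL, intervention: 5 separate + 1 joint session + 2 interviews = 8. Control: 2. Ratio 8/2 = 4.0.

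The enrolment interview precedes randomisation and is not counted. The qualitative section describes MILs with incomplete attendance as those attending fewer than 5 sessions. If 5 were the MIL total including the joint session, the ratio would be 7/2 = 3.5.

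**2. Adding contacts shared by both arms**

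The number of antenatal assessments and the timing of the MIL examination are not given, so the number of shared contacts *k* is an assumption. Ratio = (sessions + 2 + *k*)/(2 + *k*).

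| *k* | DIL | MIL |
|---|---|---|
| 0 | 5/2 = 2.5 | 8/2 = 4.0 |
| 1 | 6/3 = 2.0 | 9/3 = 3.0 |
| 4 | 9/6 = 1.5 | 12/6 = 2.0 |

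For MILs, *k* = 1 is the health examination, if it falls after randomisation. The ratio falls but stays above 1.

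**3. What this could do to recorded events**

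Assume equal true risk in both arms, an event already present before the first session, and an independent chance *q* of surfacing at each contact. The recorded fraction is 1 − (1 − *q*)^contacts. For example, with *q* = 0.1 and *k* = 0, DILs give (1 − 0.9^5)/(1 − 0.9^2) = 0.41/0.19 = 2.16. Apparent risk ratios for *q* from 0.1 to 0.5:

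| *k* | DIL | MIL |
|---|---|---|
| 0 | 2.16 to 1.29 | 3.00 to 1.33 |
| 1 | 1.73 to 1.12 | 2.26 to 1.14 |
| 4 | 1.31 to 1.01 | 1.53 to 1.02 |

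**4. Where the effect vanishes**

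Counting sessions and interviews only, an event after the last session but before the 3-month interview has 2 remaining contacts in either arm. One between 3 and 6 months has 1 in either arm. The model gives a ratio of 1 for both. An event partway through the sessions lies in between. The table in step 3 is therefore the extreme case for timing, and events nearly certain to surface behave like high *q*.

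**The case against.** **Shared monitoring.** Much safety surveillance is open to both arms. This stands. It makes 2.5 and 4 upper bounds, and with four shared contacts the apparent ratio for DILs is at most 1.31 over the range of *q* examined. It does not remove the imbalance. The article describes no set time before 3 months postpartum at which both arms are asked about safety events, and the antenatal assessments serve DILs only.

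**Symmetric interview data.** The main feared harm is violence, and that is asked of all DILs and MILs on one schedule by interviewers without access to allocation. MILs' own experience of violence is asked expressly to monitor safety, and distress scales are collected as well. This also stands. A reader might infer that the trial cannot say whether the intervention is safe, but the documents do not support that. The gap concerns the recorded events that Table 3 names as the safety measure.

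**Descriptive role.** Aim 1 carries no power target, the phase 3 criterion draws on quantitative and qualitative data together, and events may be investigated for relatedness. This limits the weight of the count. Relatedness review, however, can only judge events that reached the record.

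**Condensed article.** The questionnaires and the Incident Occurrence Reporting Form are not shown and may already hold suitable items. The point does not depend on their absence: the article itself states the measure, the source and the comparison.

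**Conclusion.** The point holds in a limited form. As written, the between-arm count of recorded safety events is open to over-ascertainment in the intervention arm. Low-severity safety alerts that depend on someone telling staff are most exposed. Pregnancy loss and hospitalisation are less affected, and violence and distress measured at interview follow the same schedule in both arms.

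The extra session contacts, 3 per DIL and 6 per MIL, come directly from the article. The contact ratios of 2.5 and 4 are upper bounds. The size of any bias is not known: the apparent ratios in the working, from 1.01 to 3.00 at equal true risk, rest on assumed detection rates, an assumed number of shared contacts and events that precede the first session.

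It would go too far to say that the comparison is distorted by a known amount. The documents show the opportunity for bias and its likely direction, not its magnitude. The change is worth making because it is cheap and safety bears on the phase 3 decision.

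**What to change.** 1. Make the main between-arm safety comparison the events elicited by one fixed set of questions in the 3- and 6-month interviews of all DILs and MILs. It could cover injury, self-harm, hospitalisation, pregnancy loss and conflict caused by the study since the previous interview. Present it with the violence and distress measures already collected there.
2. Still report all recorded events by arm, split by source of detection: intervention session, or a contact common to both arms. Interpret session-detected events as monitoring data, not as an arm contrast.
3. Record how each event was detected on the Incident Occurrence Reporting Form, if the form does not already do so.

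Real-time reporting of events is unchanged. The cost is a few interview items, possibly one form field, and revised wording for the Aim 1 analysis. There are two downsides. Recall runs over several months and may differ somewhat by arm, since sessions about violence could also affect what women report at interview. Women lost to follow-up give no interview data; the power calculation assumes 90% retention, so about 10% loss, and some could leave because of backlash. The full table of recorded events is kept alongside for that reason.

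### The printed power range for domestic violence (23% to 95%) does not follow from the trial's own inputs; the calculation that reproduces the 88% empowerment figure gives about 36% to 85%

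*Protocol article*

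**What the plan says.** All the power statements are in the protocol article, Sample size and power analysis.

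- Size: "We conducted a power analysis based on the proposed sample size of 144 dyads".
- Assumptions: the calculations were "performed assuming a significance level of 0.05, 90% retention, and no contamination".
- Empowerment indicator: with 45% of control daughters-in-law calling wife beating unjustified, "we will be able to detect a relative risk of 1.6 with 88% power".
- DV among daughters-in-law in the first six months after birth: for a relative risk of 0.5, "power ranging from 23% to 95% when the proportion reporting DV in the control arm ranges from 20% to 50" per cent.

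The DV figures are tied to the same proposed sample size. No separate test, significance level or retention rate is given for them. The section also says that the trial was not powered for a significant effect on DV. The Discussion repeats that DV power is limited, without quoting a figure.

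**The concern.** The two power statements share one set of inputs, so one calculation should give both. It gives the first and not the second. The printed DV range is also wider than a standard test produces at this size when the control proportion moves from 20% to 50%.

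This is the article's only quantitative statement of what the trial can show on DV, the outcome that the intervention is meant to change. A reader who takes the upper end at face value would think that a halving of DV would almost certainly be detected if half the control women reported it. A planner of the phase 3 trial who takes the lower end at face value would think this design weaker at low prevalence than it is.

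**Working it through.** **Inputs**

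- Allocation: equal. The Randomization section says "Within each site, dyads will be randomized to ensure treatment balance after every 20 randomizations". The Intervention and control conditions section describes "small groups consisting of 12 DILs or MILs (i.e., 6 groups of 12 individuals", and 6 × 12 = 72 = 144/2.
- Analysed per arm: 72 × 0.90 = 64.8.
- Significance level: 0.05. Sidedness is not stated; two-sided is taken first, so z = 1.96.
- Proportions: 0.45 and 0.45 × 1.6 = 0.72 for the empowerment indicator; 0.20 and 0.10, and 0.50 and 0.25, for DV at relative risk 0.5.

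**Formula** (two-proportion test, pooled variance under the null, n per arm)

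power = Φ[(|p1 − p2| − 1.96 × s0) / s1], where s0 = √(2 p̄(1 − p̄)/n), s1 = √((p1(1 − p1) + p2(1 − p2))/n) and p̄ = (p1 + p2)/2.

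**Step 1: reproduce the empowerment figure.** p̄ = 0.585, s0 = 0.0866, s1 = 0.0832. The argument is (0.27 − 1.96 × 0.0866)/0.0832 = 1.21, so power is 88.6%. Printed: 88%. One-sided, it would be 93.7%, so two-sided is the consistent reading.

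**Step 2: DV at 20% against 10%.** p̄ = 0.15, s0 = 0.0627, s1 = 0.0621. The argument is (0.10 − 1.96 × 0.0627)/0.0621 = −0.37, so power is 35.6%. Printed: 23%.

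**Step 3: DV at 50% against 25%.** p̄ = 0.375, s0 = 0.0851, s1 = 0.0822. The argument is (0.25 − 1.96 × 0.0851)/0.0822 = 1.01, so power is 84.5%. Printed: 95%.

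In between, power is about 53% at a control proportion of 30% and 70% at 40%.

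**Step 4: other ordinary methods**

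| Method | n per arm | 45% v 72% | 20% v 10% | 50% v 25% |
|---|---|---|---|---|
| Printed | – | 88% | 23% | 95% |
| Pooled, two-sided | 65 | 88.7% | 35.7% | 84.6% |
| Exact Pearson | 65 | 88.8% | 35.3% | 85.4% |
| Arcsine | 65 | 88.7% | 36.6% | 84.7% |
| Unpooled | 65 | 90.1% | 36.4% | 86.2% |
| Log relative risk | 65 | 84.7% | 34.1% | 79.8% |
| Log odds ratio | 65 | 86.8% | 34.8% | 82.6% |
| Continuity-corrected | 65 | 84.7% | 26.9% | 79.7% |
| Fisher exact | 65 | 85.2% | 27.6% | 80.9% |
| Pooled, one-sided | 65 | 93.8% | 48.1% | 91.1% |
| Pooled, no dropout | 72 | 91.6% | 38.9% | 88.1% |
| Continuity-corrected, no dropout | 72 | 88.6% | 30.2% | 84.1% |
| Fisher exact, no dropout | 72 | 88.9% | 31.6% | 84.2% |
| Pooled, one-sided, no dropout | 72 | 95.6% | 51.4% | 93.4% |
| Pooled, 130 per arm | 130 | 99.5% | 61.8% | 98.9% |

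No row gives both printed ends. Rows that come nearer to 23% fall further below 95%; rows that come nearer to 95% overshoot 23% by more.

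**Step 5: solve for the sample size.** With the pooled two-sided formula, 23% power at 20% against 10% needs about 39 per arm, and 95% at 50% against 25% needs about 95. With continuity correction the pair is 57 and 103; one-sided it is 22 and 79. Within one test a larger sample raises both ends, so no single size fits both.

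**Step 6: repeated measures.** The analytic plan mentions generalized estimating equations. As an illustration, average two visits with an assumed within-woman correlation of 0.3: the effective size is 64.8 × 2/1.3 = 99.7 per arm, and power is 51% and 96%. That comes close to the upper end but moves further from the lower one.

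**The case against.** The strongest reply is that nothing in the design rests on this sentence. The trial disclaims power for DV, DV belongs to the aim that seeks preliminary evidence, and the phase 3 criteria ask only for DV trends in the right direction. The Discussion's remark about limited power is as true at 36% to 85% as at 23% to 95%, and the printed lower end errs on the cautious side. All of that stands. It limits the consequence but does not make the figures right.

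Second, the test is not named and the 88% does not identify it uniquely. Arcsine and exact Pearson also reproduce 88% at 65 per arm; continuity-corrected, Fisher and log-relative-risk calculations do so at 72 per arm, if the stated retention is ignored. This also stands, but those last three give DV ranges of about 30% to 84%, 32% to 84% and 37% to 84%. Every method found to match 88% contradicts 23% to 95%.

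Third, the misprint may lie in the prevalence range and not in the powers. At 65 per arm, 23% and 95% correspond to control proportions of about 12.6% and 62%. The article does not show which figures are wrong, so the correction should leave room for either. For the range as printed, about 36% to 85% is the result.

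Finally, only a finite list of methods was tried. An unstated method for DV alone cannot be excluded, but the article gives no sign of one.

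**Conclusion.** The concern holds. For the printed control proportions of 20% to 50% and a relative risk of 0.5, power is about 36% to 85%. The lower end is understated by 35.6 − 23 = 12.6 points and the upper end overstated by 95 − 84.5 = 10.5 points. At 50% prevalence the type II error is 100 − 84.5 = 15.5%, about three times the implied 5%.

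This rests on equal allocation, 64.8 analysed per arm, a two-sided 0.05 level and a single comparison of proportions. The first three come from the article's text or from matching its 88%; the last is the ordinary reading of the section. It is a wrong printed figure with modest consequence: the empowerment power figure stands, and neither enrolment nor the phase 3 criteria depend on the DV range.

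**What to change.** Replace the DV sentence with one that says: power to detect a relative risk of 0.5 ranges from about 36% to about 85% as the control proportion goes from 20% to 50% (two-sided 0.05, 65 analysed per arm). Name the test once, for both power statements.

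If another test, a repeated-measures calculation or a different prevalence range was intended, state it and recompute both DV ends on that basis. If the test changes, recompute the 88% figure with it.

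The cost is one sentence and a less favourable upper figure. Sample size, enrolment and analysis do not change.
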